## Abstract

**Background:**

The eye is well known to be sensitive to clearly high doses (>2 Gy) of ionizing radiation. In recent years, however, cataracts have been observed in populations exposed to lower doses. Interventional cardiologists are repeatedly and acutely exposed to scattered ionizing radiation (X-rays) during the diagnostic and therapeutic procedures they perform. These "low" exposures may cause damage to the lens of the eye and induce early cataracts, known as radiation-induced cataracts. The O'CLOC study (Occupational Cataracts and Lens Opacities in interventional Cardiology) was designed to test the hypothesis that interventional cardiologists, compared with an unexposed reference group of non-interventional cardiologists, have an increased risk of cataracts.

**Method/Design:**

The O'CLOC study is a cross-sectional study that will include a total of 300 cardiologists aged at least 40 years: one group of exposed interventional cardiologists and another of non-interventional cardiologists. The groups will be matched for age and sex. Individual information, including risk factors for cataracts (age, diabetes, myopia, etc.), will be collected during a telephone interview. A specific section of the questionnaire for the exposed group focuses on occupational history, including a description of the procedures (type, frequency, radiation protection tool) used. These data will be used to classify subjects into "exposure level" groups according to cumulative dose estimates. Eye examinations for all participants will be performed to detect cataracts, even in the early stages (lens opacities, according to LOCS III, the international standard classification).  The analysis will provide an estimation of the cataract risk in interventional cardiology compared with the unexposed reference group, while taking other risk factors into account. An analysis comparing the risks according to level of exposure is also planned.

**Discussion:**

This epidemiological study will provide further evidence about the potential risk of radiation-induced cataracts at low doses and contribute to cardiologists' awareness of the importance of radiation protection.

**Trial Registration:**

NCT01061463

## Background

Although the sensitivity of the lens of the eye to high doses of ionizing radiation (IR) is well known, considerable uncertainty surrounds the relation between radiation dose and cataracts. The radiation protection standards formulated by the United States National Council on Radiation Protection (NCRP) and the International Commission on Radiological Protection (ICRP) [1] are all based on the assumption that lens opacities (cataracts) are deterministic radiation-induced effects and appear only if a dose threshold is exceeded [1,2]. The current dose thresholds for radiation-induced lens opacities are 2 Gy for a single dose or 5 Gy for fractionated doses. However, several recent studies have now raised questions about this assumption [3] (UNSCEAR (United Nations Scientific Committee on the Effects of Atomic Radiation) 2008 Report: *"Sources of ionizing radiation"*.). Epidemiological and experimental studies appear to show the formation of radiation-induced cataracts at much lower doses than the current standards and strongly suggest a stochastic hypothesis (non-threshold effect) [4].

### Radiation-induced cataracts in populations with low levels of radiation exposure

While posterior subcapsular cataracts are characteristic of radiation exposure, several sets of data suggest that the broader category of posterior cortical cataracts may also be regarded as radiation-associated. Increased risks of lens opacities (including posterior subcapsular, cortical, nuclear, and mixed cataracts) have been reported in different populations for the lower doses induced by chronic, fractionated, or acute exposure to γ or neutron radiation, β particles, galactic cosmic radiation, and X-rays (Table 1). An increased frequency of radiation-induced lens opacities has also been observed in a variety of environmental, medical, and occupational contexts. Reports of lens opacities related to environmental exposure come from the Hiroshima and Nagasaki survivors [5-7], from children living in the contaminated territories of Chernobyl [8], and residents of (60)Co-contaminated buildings in Taiwan [9]. Sources of medical exposure include X-Ray exposure during computed tomography [10] and radiotherapy [11,12]. Occupational exposure to IR and lens opacities have been reported for Chernobyl clean-up workers [13], astronauts [14-16] and pilots [17], and medical personnel, such as radiology technicians [18]. Nonetheless, new data from exposed human populations are still necessary to confirm the absence of a dose threshold, or the need to revise the existing threshold.

**Table 1 T1:** Main epidemiological studies of low dose radiation-induced cataracts

	Population size	Exposure level	Exposure age or period	Eye examination age or period	Type of cataracts involved
**Hiroshima and Nagasaki survivors**					
*Otake et al. *[5]	Cohort of 1983 individuals	-	H & N: Mean age = 29.3 yrs and 23.4 yrs	1963-1964	γ-ray threshold: 730 mGy neutron-ray threshold: 60 mGy
*Minamoto et al.*[6]	Cohort of 873 individuals	Eye dose= 405 mSv	Mean age = 8.8 yrs	Mean age = 64.8 yrs	Cortical opacities PS opacities
*Nakashima et al.*[7]	Cohort of 730 individuals	-	Median age = 10.5 yrs	Median age = 66.6 yrs	Threshold dose: 0.6 Sv for cortical opacities 0.7 Sv for PS cataracts

**Chernobyl children**					
*Day et al.*[8]	996 exposed/791 unexposed	-	Chronic	Range = 5 - 17 yrs	PS opacities

**Contaminated buildings in Taiwan**					
*Chen et al.*[9]	Cohort of 114 individuals	161.9 mSv	Chronic	Mean= 24.8 yrs	Focal lens defects

**Diagnostic examinations**					
*Klein et al.*[10]	4926 subjects	Diagnostic X-Ray exposure	-	Range = 43 - 84 yrs	PS opacities

**Treatment of benign diseases**					
*Wilde et al.*[12]	20 adults treated by radium irradiation	Range: 1-8 Gy	Median age = 6 months	Range = 31 - 46 yrs	Subcapsular punctuate opacities at 100 mGy
*Hall et al. *[11]	483 individuals treated by radiotherapy vs. 89 controls	0.4 Gy (0-8.4)	Mean age = 5 months	Range = 36 - 54 yrs	PS opacities and Cortical opacities

**Chernobyl Liquidators**					
*Worgul et al.*[13]	8,607 Ukrainian workers	Median lens dose = 120 mGy (0-0.8)	Mean age = 36.7 yrs	Mean = 45 yrs	PS changes and Cortical cataracts

**Astronauts**					
*Cucinotta et al*[14]	295 astronauts	Mean eye dose = 3.6 mSv	Chronic (at least 40 yrs old at first flight)	First eye exam in 1977	PS cataracts, Nuclear cataracts and mixed
*Rastegar et al.*[15]	21 astronauts vs. 395 unexposed	-	Mean time in space = 62 days	Mean = 59 yrs in astronauts group	Opacities in posterior capsule
*Chylack et al.*[16]	171 astronauts vs. 247 unexposed	Lens dose = 15.1 to 129.3 mSv	-	2004-2006	Cortical cataracts and PS opacities

**Airline pilots**					
*Rafnsonn et al.*[17]	274 pilots with lens opacities vs. 374 controls	Cumulative dose: 0 to 48 mSv	-	Mean = 75 yrs in cases; 66.1 yrs in controls	Nuclear cataract

**Radiologists and radiological technologists**					
*Chodick et al.*[18]	Cohort of 35 705 radiology technicians	Median = 28.1 mGy	Range = 24 - 44 yrs	Follow up between 1983 and 2004	Any cataract

PSC: posterior subcapsular cataract; PS: posterior subcapsular;

### Interventional cardiologists: a little-studied exposed population

The widespread use of IR in medical practice for both diagnostic and therapeutic purposes results in a significant increase in exposure of both patients and medical staff [19]. The use of medical imaging involving X-rays as a diagnostic tool or during interventional procedures has increased steadily over the last few years, particularly in the field of interventional cardiology, including cardiac electrophysiology [20,21]. Interventional cardiologists are now thought to be the most highly exposed of all medical personel [22-24]. The ablation of atrial fibrillation performed by electrophysiologists, for example, is a long and potentially irradiating procedure [25], and the operator's eyes are exposed to scattered X-rays. The frequent failure of some cardiologists to use protective leaded eyewear helps explain the crucial need for radiation monitoring and risk assessment for medical staff [26]. Interventional cardiologists are exposed to risks in the same range as those for which early-stage cataracts have been observed.

Very few epidemiological studies have been published on the risk of cataracts in interventional radiology (including procedures for interventional cardiology). Junk *et al. *[27] took a first step towards identifying and increasing awareness of these risks in a study that screened 59 volunteer participants at a professional meeting of interventional radiologists, including cardiologists. They observed a surprisingly high frequency of posterior subcapsular cataracts in their sample: 22 individuals (37.3%) had small paracentral dot-like opacities in the posterior subcapsular region of the lens, consistent with early signs of radiation damage, and five more (8%) had diagnoses of cataracts (corresponding to more advanced stages of lens opacities). This study nevertheless had limitations: a selection bias due to their recruitment method, which may have resulted in overestimating prevalence, and the absence of a control group of unexposed participants. A study presented at the European Society of Cardiology congress in 2009 [28] did use both an exposed and a control group and found a significant difference in the frequency of lens opacities (37.9% vs. 12%, p < 0.005). These findings reinforced the results reported by Junk *et al. *Nevertheless, as the authors underlined, their study also had methodological limitations, including the same potential selection bias described for Junk *et al. *and an age difference between exposed and unexposed group that may partly account for the results (46.7 vs. 40.5 years). A recent study examined the prevalence of radiation-associated posterior lens opacities among 56 interventional cardiologists and 22 controls: 52% of the former had lens opacities and only 9% of the latter [29]. Overall, relatively few cataracts have been reported among medical staff in interventional radiology, although some authors have stressed the lack of adequate monitoring [30].

In conclusion, a few studies have examined cataracts among interventional cardiologists, but the cause of the early cataracts identified has not been completely investigated. An epidemiological study in this population should provide further knowledge about the potential risk of radiation-induced cataracts in populations with exposure levels thus far considered to be low and should also improve cardiologists' awareness of the need for radiation protection. For these reasons, the Institut de Radioprotection et de Sûreté Nucléaire, with the cooperation of interventional cardiology groups of the French Society of Cardiology, has launched the O'CLOC study (Occupational Cataracts and Lens Opacities in Interventional Cardiology), designed to test the existence of an increased risk of cataracts among interventional cardiologists, compared with a control group of cardiologists not exposed to X-rays.

## Method/Design

### Study Aims

The aim of the O'CLOC study is to compare the prevalence of different stages and types of cataracts (from no opacities to severe cataracts; nuclear, cortical or posterior subcapsular) in an exposed group of interventional cardiologists with an unexposed reference group of non-interventional cardiologists, while taking into account other risk factors for cataracts, use of radiation protection tools, and exposure level.

### Population and selection

There are approximately 1700 interventional cardiologists in France: 1000 coronary interventional cardiologists (CICs) and 700 cardiologists specializing in the treatment of cardiac arrhythmias (arrhythmologists or electrophysiologists). Stratification of recruitment according to this distribution of CICs and electrophysiologists make this study the first to study both types of cardiologists exposed to X-Rays. It should therefore be as representative as possible - at least in terms of proportion - of interventional cardiology in France.

The relative youth of the population of cardiologists has presented difficulties previously in studying cataracts in this group, specifically, the absence of data about lens opacities either in the general population for the same age class as cardiologists who could be considered as unexposed (most data concern essentially "senile cataracts"), or in an appropriate control group. That is, information about the background frequency of lens opacities in a reference population is essential. This study will compare a group of exposed individuals (interventional cardiologists chronically exposed to X-rays) to a group of unexposed but otherwise comparable individuals: cardiologists not occupationally exposed to ionizing radiation (non-interventional cardiologists). The O'CLOC design is presented in Figure 1. French centres employing CICs and arrhythmologists will be selected according to several criteria: employment of at least two interventional cardiologists; balanced distribution of the centres across France; a balanced distribution of public and private hospitals. All cardiologists in the selected centres will be contacted and invited to participate. Only cardiologists at least 40 years old will be included. This age criterion was chosen to ensure occupational exposure to IR for at least 10 years in the exposed group. Subjects with a history of personal medical radiation exposure (radiotherapy, brain scans) will be excluded from both groups. Moreover, non-interventional cardiologists with a cumulative significant history of work in interventional cardiology above one year will also be excluded. To ensure comparability between the exposed and unexposed groups, subjects will be matched by sex and age.

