### Data collection

#### Questionnaires

Trained interviewers, blinded to the participants' lens opacity status, will collect all the rest of the data. Individual information will be collected about general characteristics, potential risk factors for cataracts, and history of exposure to medical radiation, both personally and occupationally. The occupational exposure data will be collected in a specific part of the questionnaire (see Table 2) that trained interviewers will use to ask the interventional cardiologists about their lifetime occupational activity. This section specifically mentions most common types of procedures: for the CICs, coronary angiography and coronary angioplasty, and for the electrophysiologists, pacemaker or intracardiac defibrillator implantation, pacemaker or intracardiac defibrillator resynchronization, radiofrequency catheter ablation except for atrial fibrillation, and radiofrequency catheter ablation of atrial fibrillation. These distinctions are justified by substantial differences in doses delivered and received by cardiologists [24].

**Table 2 T2:** Items collected in the questionnaire

Medical information
Weight
Size
Colour of the eyes
Left or Right handed
Smoking status
Diabetes
Myopia
Corticosteroids intake
History of cancer and radiotherapy
History of treated cataract
History of eye traumatism
Congenital cataract
History of CT scans and localisation
History of significant occupational exposure to ionising radiation for more than 12 consecutive months

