**Occupational history**

List of all centres and periods of activity
For each period, precise:
Coronary angiography?
Mean number of procedures per week or year
Radial or femoral access route
Coronary angioplasty?
Mean number of procedures per week or year
Radial or femoral access route
Pacemaker or intracardiac defibrillator: implantation ?
Mean number of procedures per week or year
Mean fluoroscopy time per procedure
Pacemaker or intracardiac defibrillator: resynchronisation?
Mean number of procedures per week or year
Mean fluroscopy time per procedure
Radiofrequency catheter ablation except atrial fibrillation ?
Mean number of procedures per week or year
Mean fluroscopy time per procedure
Radiofrequency catheter ablation of atrial fibrillation?
Mean number of procedures per week or year
Mean fluroscopy time per procedure
Frequency of use of radiation protection tools:
Lead apron
Lead thyroid shield
Lead eye glasses (goggles)
Other eye protection
Lead gloves
Protective mobile screen
Radiation protection cabin
Frequency of use of dosimetric badge

To supplement and verify the information collected in the occupational questionnaire, we will use data from the *SISERI System (Systéme d'Information de la Surveillance de l'Exposition aux Rayonnement Ionisants)*, an information system recording occupational dosimetry of potentially exposed French workers, centralized at the IRSN. SISERI will make it possible for us to confirm the occupationally-exposed or unexposed status of the cardiologists enrolled in the O'CLOC study. In particular, we will be able to confirm the unexposed status of eligible non-interventional cardiologists, by their absence from the database or their presence for less than 12 months. SISERI will also provide us with information on individual dosimetry monitoring (based on dosimetry badges used under the lead apron). Depending on the reliability of the doses recorded there, it may also provide us a crude estimation of doses received by cardiologists.

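### Three differently worded 12-month rules define the unexposed group, and the questionnaire as listed cannot add up a control's separate periods of interventional work

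*Protocol article*

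**What the plan says.** The protocol article sets a duration limit for the unexposed group in three places.

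- **Population and selection** gives the eligibility rule: "non-interventional cardiologists with a cumulative significant history of work in interventional cardiology above one year will also be excluded". The count is cumulative and the subject is interventional cardiology.
- **Table 2, medical information** lists the item "History of significant occupational exposure to ionising radiation for more than 12 consecutive months". The count is consecutive and the subject is ionising radiation at work in general.
- **The SISERI paragraph after Table 2** says the register will be used to "confirm the unexposed status of eligible non-interventional cardiologists", "by their absence from the database or their presence for less than 12 months". It does not say whether the months are summed or continuous.

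The article describes the detailed occupational section as addressed to one group. The abstract says "A specific section of the questionnaire for the exposed group focuses on occupational history". The Questionnaires section describes it as the part that "trained interviewers will use to ask the interventional cardiologists about their lifetime occupational activity". SISERI supplies "individual dosimetry monitoring (based on dosimetry badges used under the lead apron" worn by the cardiologist.

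**The concern.** A study of this kind depends on a clean reference group. Population and selection itself treats the background frequency of opacities as essential, and the Planned analysis uses the same unexposed group as the reference for the dose-response analysis. If the instrument that applies the exclusion asks a narrower question than the exclusion itself, some people whom the rule should remove remain as controls.

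This is plausible here. Centres are selected because they employ at least two interventional cardiologists, and every cardiologist in them is invited. Some non-interventional cardiologists in such centres may have done interventional work in separate spells. If exposure raises the risk of opacities, keeping them lifts the control prevalence and shrinks both contrasts.

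**Working it through.** **1. The rules side by side.** Take a non-interventional cardiologist with two separate 11-month periods of interventional work.

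| Source | Rule | Result |
|---|---|---|
| Population and selection | cumulative, above one year | 11 + 11 = 22 months: excluded |
| Table 2 item | more than 12 consecutive months | longest spell 11 months: answers no |
| SISERI, months summed, both periods recorded | less than 12 months | 22 months: not confirmed as unexposed |
| SISERI, months taken as one continuous run | less than 12 months | 11 months: confirmed as unexposed |
| SISERI, neither period recorded | absent from the register | confirmed as unexposed |

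The rules disagree, and SISERI settles the matter only on one reading and only if the periods were recorded. A single spell longer than 12 months is caught by the Table 2 item. The gap is several spells of at most 12 months each, adding to more than a year, and missed by SISERI. The listed items give no total for a control, because the list of periods belongs to the section described for the exposed group.

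**2. The plan's own sample sizes.** Inputs from Sample size considerations: 80% power, p < 0.05 (taken as two-sided) and the four pairs of prevalences. The arcsine formula is n = (1.960 + 0.842)² / [2(asin√p1 − asin√p2)²].

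| p1 vs p2 | Computed n per group | Stated |
|---|---|---|
| 8% vs 1.5% | 145.96 | 146 |
| 37.9% vs 12% | 40.98 | 40 |
| 52% vs 9% | 15.65 | 16 |
| 23% vs 10% | 123.27 | 123 |

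The stated figures reproduce, to within one subject.

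**3. Effect of exposed controls who stay in.** Let c be the share of controls affected and f the fraction of the excess risk that they carry. The control prevalence becomes p2 + c·f·(p1 − p2). The documents give neither c nor f; both are assumptions. With c = 10%:

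- 8% vs 1.5%, f = 0.1: 0.015 + 0.1 × 0.1 × 0.065 = 0.01565
- 8% vs 1.5%, f = 1: 0.015 + 0.1 × 0.065 = 0.0215
- 23% vs 10%, f = 0.1: 0.10 + 0.1 × 0.1 × 0.13 = 0.1013
- 23% vs 10%, f = 1: 0.10 + 0.1 × 0.13 = 0.113

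Power of the two-sided chi-square test at 150 per group, by exact enumeration of the two binomial distributions, without matching or adjustment:

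| Contrast | None affected | c = 10%, f = 0.1 | c = 10%, f = 0.25 | c = 10%, f = 0.5 | c = 10%, f = 1 |
|---|---|---|---|---|---|
| 8% vs 1.5% | 79.7% | 78.5% | 76.5% | 73.1% | 66.1% |
| 23% vs 10% | 86.9% | 86.1% | 84.9% | 82.6% | 77.7% |

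The prevalence ratio moves from 0.08/0.015 = 5.33 to 0.08/0.01565 = 5.11 (f = 0.1) or 0.08/0.0215 = 3.72 (f = 1). In the second contrast it moves from 0.23/0.10 = 2.30 to 0.23/0.1013 = 2.27 or 0.23/0.113 = 2.04. If only 2% of controls were affected and carried the whole excess, power would be 77.1% and 85.3%.

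**The case against.** The strongest reply is that the exclusion is not left to the Table 2 item. SISERI is named as a check on exactly this status, the word consecutive does not appear there, and presence in a register is naturally read as total time. On that reading the 22-month example fails the check if both periods were recorded. Table 2 also gives short labels in a condensed article, not the questionnaire's wording, and an eligibility screen that the article does not describe may precede the SISERI check. This stands as far as it goes. A reader might infer that the exclusion cannot be applied at all, and the documents do not support that.

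It does not remove the inconsistency. The article chose to state both cumulative and consecutive, and it leaves the SISERI count open. SISERI's individual monitoring comes from badges, so absence from it is weaker evidence than a reported work history.

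Two further inferences are tempting and should not be drawn. The background remark that "some authors have stressed the lack of adequate monitoring" concerns medical staff in interventional radiology and does not mention SISERI, so it does not show that the register is incomplete. The article also gives no reason for asking how often badges are used, so the item is not an admission that they go unworn. The caveat on reliability concerns recorded doses, not whether a person appears in the register.

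On size, the objection is right that 10% of controls carrying the full exposed prevalence is a worst case. The age limit is meant to give the exposed at least 10 years of exposure, whereas a missed control may have under two.

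**Conclusion.** The point holds in a limited form. The three statements of the rule differ, and the questionnaire as listed cannot identify a control whose shorter spells add to more than a year. The exclusion can therefore be applied in part, but not in full as written. If exposure raises risk, the error runs toward no difference in both the main and the dose-response comparison.

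Its size cannot be known from the documents. With an assumed 10% of controls affected, the loss of power runs from about 1 percentage point in either contrast (one tenth of the excess) to about 14 points for 8% versus 1.5% and 9 points for 23% versus 10% (all of the excess). The first contrast has no power to spare at 150 per group, so any loss takes it further below 80%. The reason to act is that the mismatch is plain in the text and cheap to remove, not that a large bias has been shown.

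**What to change.** 1. Reword the Table 2 item to ask for the total number of months, all periods added, of interventional or fluoroscopy work, and put it to the non-interventional group.
2. Apply the cumulative one-year rule in Population and selection to that total.
3. State that SISERI months are counted cumulatively, and that absence from SISERI does not override a reported total above one year.
4. Ask the reworded item of the 30 non-interventional cardiologists recruited by April 2010. The other 120 of the planned 150 can be asked it at interview.

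The cost is one reworded item, about 30 short call-backs and a few more exclusions, which would need replacing to keep 150 in the group.
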